### Statistical analysis

#### Clinical effectiveness, acceptability and perceived benefit analysis

Effectiveness outcomes (Primary Aim 1), including the proportion of women identified at particular psychosocial risk levels (as defined in the SAFE START and PIPA models of care) and proportion of women considered to be ‘correct’ or ‘incorrect’ referrals in each care model will be analysed using chi-square and independent-samples *t*-tests (or Mann Whitney U tests, as appropriate). This approach will also be used to examine the acceptability and perceived benefit of the SAFE START and PIPA models (Primary Aim 3). Initial checking of statistical assumptions (normality, multicollinearity, examination of outliers) will be undertaken. Chi-square analysis of subgroups of women based on risk status may also be explored. Clinically significant differences between the two models will be based upon obtaining at least medium effect sizes or absolute percentage differences of at least 15%.

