**Methods:**

This is a comparative-effectiveness study comparing ‘care as usual’ to an alternative model sequentially over two 12-month periods. Data will be collected from women at Time 1 (initial antenatal psychosocial assessment), Time 2 (2-weeks after Time 1) and from clinicians at Time 3 for each condition. Primary aims will be evaluated using a between-groups design, and the secondary aim using a within group design.

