### Design

This is a comparative-effectiveness study which will compare ‘care as usual’ (the SAFE START model) to an alternative model (the PIPA model) sequentially over a 36 month period (see Fig. 2). It will employ a mixed methods design. The primary aims will be evaluated using a between-groups design, comparing the two models of care on a range of outcomes. The secondary aims will be evaluated using a within group design.

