### Setting

The site for the PIPA Project is the Royal Hospital for Women (RHW), a large teaching hospital in metropolitan Sydney, Australia, with approximately 4000 births per year [26].

During the first 12 months of the PIPA Project, women who attend the participating site for their first midwife-led routine antenatal visit will receive care as usual (SAFE START model), while women who attend for their antenatal booking-in visit in the last 12 months of the study will receive the alternative PIPA model of care. There will be an interval of approximately 12 months to allow for the implementation of a new state-wide administrative database (eMaternity), which will incorporate the PIPA model and one month of staff training for the PIPA model. During this time, women attending the hospital will continue to receive care as usual, though no study data will be collected (see Fig. 2).

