### Data sources, measures and procedures

#### Time 1: Initial psychosocial assessment conducted at the antenatal ‘booking in’ visit

The hospital data management system (ObstetriX and subsequently eMaternity) will be used to identify all women who attended the participating site during the data collection periods for the PIPA Project, and for whom a routine psychosocial assessment was completed. The Time 1 dataset will include: date of booking in visit and psychosocial assessment; gestation and maternal age at this time; maternal date of birth; estimated date of delivery; partner status; gravidity (including reason for pregnancy loss, where available); parity; country of birth; physical health conditions; type of conception; model of maternity care; EPDS: total and Q10 scores; EPDS: item level responses (SAFE START only); psychosocial questions: item level responses; psychosocial questions: total score (PIPA only); referral/s indicated as a result of the psychosocial assessment (yes/no); referral/s indicated as a result of the psychosocial assessment (specified; PIPA only); language; interpreter needed; financial class (public, private or overseas patient); and Time 2 Expression of Interest response (yes/no). Time 1 data will be extracted by the data manager at the participating site at approximately weekly intervals, for all women allocated to the SAFE START and PIPA models of care.

#### Time 2: Two weeks post-time 1

Women who consent to participation at Time 2 will complete the EPDS [6], the ‘Whooley’ questions [19] followed by a third ‘help’ question [20], the Generalized Anxiety Disorder Scale [GAD-7] [21], the Matthey Generic Mood Questionnaire (MGMQ) [22], an ‘interval’ question to assess perceived change in emotional wellbeing at Time 2 [27] and the Mini International Neuropsychiatric Interview v6.0 [M.I.N.I.; mood and anxiety disorder modules only] [23]. Women will also complete a short survey covering the acceptability of the psychosocial questions and assessment process.

‘Key Survey’™ will be used as the platform for data collection for all Time 2 measures *except* the M.I.N.I., which will be collected using infrastructure provided by Medical Outcomes Systems (to whom the online M.I.N.I. is copyrighted). Alternatively, these questionnaires will be administered by phone by the Research Officer verbatim, with participant responses captured in the project-specific ‘Key Survey’ and MINI instruments.

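### Two non-randomised cohorts about 24 months apart are compared with unadjusted tests only, so case-mix and calendar change cannot be separated from the effect of PIPA

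*Protocol article*

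**What the plan says.** The Methods paragraph of the abstract describes care as usual compared with an "alternative model sequentially over two 12-month periods". The Design section places these within a longer span: "sequentially over a 36 month period". According to Setting, SAFE START is given in the first 12 months and PIPA in the last 12, at a single hospital. In the year between them the administrative database is replaced and usual care continues, "though no study data will be collected". The Time 1 section confirms the change of source: "The hospital data management system (ObstetriX and subsequently eMaternity) will be used to identify all women who attended the participating site".

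The section on clinical effectiveness, acceptability and perceived benefit fixes the tests. Proportions at each risk level and proportions of correct and incorrect "referrals in each care model will be analysed using chi-square and independent-samples" tests, or Mann-Whitney tests. Acceptability and perceived benefit (Primary Aim 3) are handled the same way. The section calls a difference clinically significant if it reaches a medium effect size or at least 15 percentage points.

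The Time 1 section lists what is extracted for both cohorts, including "gestation and maternal age at this time; maternal date of birth; estimated date of delivery; partner status", together with parity, country of birth, language, need for an interpreter, financial class and model of maternity care. None of these enters the stated analysis.

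**The concern.** Nothing in the allocation balances the two cohorts. If the women who book in during Year 3 differ from those in Year 1, or if local referral habits change over the interval, a crude comparison puts that change into the PIPA estimate. The hypotheses credit the difference to the model, and the article does not discuss confounding by period.

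The stated stratification does not repair this. Primary Aim 1(i) is stratified by comparable risk levels, and chi-square tests within risk subgroups may be explored. Those levels are produced by the models themselves (three under SAFE START, six under PIPA, from different instruments and cut-offs, Table 1), so they are not a common baseline measure. For Aims 1(ii) and 3 the plan commits to no stratification.

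Aim 3 has a further exposure. Only about 15-20% of English-speaking women are expected at Time 2, and the Fig. 2 notes list staffing limits and the expression of interest not being asked among the reasons for exclusion. These could differ between the two years.

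The same crude effects enter the incremental cost-effectiveness ratios and the budget impact analysis.

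**Working it through.** **Sample sizes in the plan.** Participant eligibility and expected sample sizes gives about 4000 births a year and about 85% assessed: 4000 × 0.85 = 3400 per 12 months, close to the stated 3500 per model. Time 2: 15% to 20% of 3400 is 510 to 680, which covers the stated 650 per model (the share of English speakers is not given). The same section lists 120 social work, 120 mental health midwife and 50 MCD referrals for each model: 120 + 120 + 50 = 290, if none overlap. No alpha or power is stated.

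**Separation in time.** Year 1 is centred at month 6 and Year 3 at month 30: 30 − 6 = 24 months between midpoints. The gap from end to start is about 12 months.

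**Chance that a spurious shift is significant.** Assumptions: base proportion 60% (not tied to any outcome in the article), two-sided 5% test, no PIPA effect, shift d. SE = √(2 × 0.6 × 0.4 / n), and rejection probability = Φ(d/SE − 1.96) + Φ(−d/SE − 1.96).

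| n per model | SE | d = 2 points | d = 3 points | d = 5 points |
|---|---|---|---|---|
| 3500 (Time 1) | 0.0117 | 40% | 73% | 99% |
| 650 (Aim 3, women) | 0.0272 | 11% | 20% | 45% |
| 290 (rated referrals) | 0.0407 | 8% | 11% | 23% |

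At an assumed 30% base the n = 3500 row becomes 44%, 77% and 99%, so the result depends little on that choice.

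**How case-mix alone produces such a shift.** Suppose 10% of low-risk and 50% of high-risk women are referred under both models. If the high-risk share is 30%, the crude rate is 0.10 + 0.40 × 0.30 = 22%. At 35% it is 24%, and at 40% it is 26%. With 3500 per model, the moves from 22% to 24% and from 22% to 26% are significant in 51% and 97.5% of studies, although the difference within each risk group is zero. Adjustment for that factor would remove it.

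**Against the 15-point criterion.** For true rates a and b, SE = √([a(1 − a) + b(1 − b)]/n).
- 5 points of drift and no effect (60% against 65%): the chance of observing 15 points or more is 1 − Φ(0.10/SE). It is essentially 0 at n = 3500 (SE 0.0116), about 0.01% at n = 650 (SE 0.0268) and about 0.6% at n = 290 (SE 0.0402).
- True effect of 10 points and no drift (60% against 70%): 1 − Φ(0.05/SE) is about 0.001%, 3% and 10% at the three sizes.
- The same effect plus 5 points of drift: the expected crude difference is 10 + 5 = 15, so the chance is 50% at every size. Drift of 5 points the other way turns a true 15 into an expected 10.

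**The case against.** The strongest defence is the plan's own threshold. A reader might infer from the 99% figure that drift would lead the plan to declare PIPA better. The documents do not support that: the plan asks for 15 points or a medium effect size, and 5 points of drift alone almost never reaches 15 at 3500, 650 or 290 per model. What remains is bias in the estimate, which matters when the true effect lies near the threshold. The medium effect size is not defined for proportions, so the protection it gives is uncertain.

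A reader might also extend the n = 3500 row to Primary Aim 3. That does not hold: Aim 3 rests on about 650 women per model and an estimated 25 provider surveys.

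A third tempting reading is that regression would remove all the confounding. It removes measured case-mix only. Each model has one period and one platform, and PIPA is built into eMaternity, so the platform is partly the intervention.

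Finally, this is a condensed article, and its mention of checking multicollinearity may hint at multivariable modelling. A covariate list can fairly be left to the full plan. However, the article names the tests for the primary aims, and those are unadjusted, so this is a stated choice and not an omission.

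**Conclusion.** The concern stands in a limited form. As written, the analysis of Primary Aims 1 and 3 cannot separate measured case-mix differences or calendar change from the effect of PIPA, and the risk-level strata do not solve this. Statistical significance is most exposed in the full Time 1 cohort; in the smaller samples the same bias is present but is less often significant. The percentages rest on an assumed base rate, an assumed 5% level and assumed shifts, because the article gives no figures for drift. They show sensitivity to drift and do not predict that drift will occur. The 15-point criterion limits false claims of clinical benefit from drift alone but does not protect the estimate, the reading of effects near the threshold, or the cost-effectiveness ratios.

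**What to change.** - **Main analysis.** For the woman-level outcomes of Aims 1 and 3, use regression (logistic for proportions), reported as an adjusted absolute risk difference with 95% CI. Judge the 15-point criterion on that estimate.
- **Covariates.** Adjust for the Time 1 variables held for both cohorts that the model of care cannot affect: age, parity, partner status, country of birth, language or interpreter need, financial class, model of maternity care and gestation at booking. Leave Time 1 EPDS out of the main set: under SAFE START it is completed on paper and scored by hand, and under PIPA it is administered by the midwife and scored automatically.
- **Crude tests.** Keep them as secondary results, and as the analysis for provider outcomes, which women's covariates cannot adjust.
- **Referral correctness.** Apply the adjustment where ratings can be linked to Time 1 records. The article describes those records as de-identified and the ratings as collated separately at meetings, and it describes no link; the sponsor should confirm whether one exists.
- **Time.** Show outcomes by booking month within each period as a descriptive check. State that calendar time and platform coincide with the model, so residual confounding cannot be removed.

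The cost is revised analysis wording, modest programming, a record-linkage step for correctness ratings and a slightly more complex headline estimate. Unmeasured confounding remains. According to Study status, PIPA data collection had not begun, so at that point the change could be fixed before any PIPA outcome was seen.

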#### Cost-effectiveness analysis

The primary outcome variable for the cost-effectiveness analysis (Primary Aim 2) will be the proportion of ‘correct’ referrals initiated and ‘incorrect’ referrals averted. The incremental costs and effects of SAFE START compared to PIPA will be expressed as the incremental cost-effectiveness ratio (ICER). The ICER combines the net changes in effects with the net change in costs between two strategies providing a relative estimate of the cost-effectiveness of the PIPA program relative to the SAFE START program. The ICER per ‘correct’ referral made and per ‘incorrect’ referral averted will be estimated using mean costs and effects and represented with 95% confidence intervals for the ICERs using non-parametric bootstrapping techniques. One-way and multivariate probability sensitivity analysis using Monte Carlo simulations across the cost and effect distributions will be undertaken to investigate uncertainty around the ICERs. Based on number of women screened and proportion of ‘correct’ and ‘incorrect’ referrals identified, the economic evaluation will allow a budget impact analysis to be undertaken to determine the costs of running SAFE START and PIPA at other maternity hospitals.

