**Fig. 1 Fig1:**
[figure not shown]
Psychosocial care pathway

For the purposes of the PIPA Project, the following definitions will apply:

*Referral:* will be defined as the initial referral made by the midwife to one or more of the on-site support options. *NOTE: Referrals to services external to the participating site are outside the scope of data collection for the current project, as are referrals made at later antenatal appointments (*i.e.*, not the initial booking-in appointment).*

*‘Correct’ referral:* a clinically appropriate referral made by the midwife, as determined by the consensus opinion of senior psychosocial clinicians at the weekly ‘triage’ and MCD meetings.

*‘Incorrect’ referral:* a clinically inappropriate referral made by the midwife, as determined by the consensus opinion of senior psychosocial clinicians at the weekly ‘triage’ and MCD meetings.

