^b^‘Complex’ risk factors : homelessness or housing instability; domestic violence; substance misuse; contact with child protection services

^c^‘Social’ risk factors: young maternal age (less than 20 years); no partner; booking-in appointment at >20 weeks gestation

**Table 2 Tab2:** Data collection schedule and measures

Measure	Time 1 *All women (routinely collected data)*	Time 2 *Consenting women only*	Time 3 *Health professionals only*
Demographic information^a^	X		
EPDS^a^	X	X	
Psychosocial assessment^a^	X		
Routine referral information^b,c^	X		
Feedback survey (women)^d^		X	
Costing data	X		X
Feedback survey; observational data; key informant interviews; focus groups (health professionals)^b,c,e^			X
Whooley questions^f^		X	
GAD-2^f,g^		X	
MGMQ^f,g^		X	
MINI^f,g^		X	
Interval question^f,g^		X	
Brief help seeking items^f,g^		X	

*EPDS* Edinburgh Perinatal Depression Scale, *GAD-2* Generalized Anxiety Disorder Scale-2items, *MGMQ* Matthey Generic Mood Questionnaire, *MINI* Mini International Neuropsychiatric Interview (v6.0; mood and anxiety disorder modules only; Data will be used to address: ^a^All aims; ^b^Primary Aim 1 (clinical effectiveness); ^c^Primary Aim 2 (cost effectiveness); ^d^Primary Aim 3 (pregnant women perspectives); ^e^Primary Aim 3 (health care provider perspectives); ^f^Secondary Aim (psychometric evaluation). ^g^Completed by women allocated to the PIPA model of care only

*Primary Aim 2: Cost-effectiveness outcomes:* To quantify: i) the cost per ‘correct’ and ‘incorrect’ referral made at the initial psychosocial assessment, for each model of care; ii) the incremental cost per ‘correct’ referral made and the incremental cost per ‘incorrect’ referral averted by the PIPA model compared to the SAFE START model; and, iii) the budgetary implications of implementing the PIPA model at the participating site, based on number of women assessed.

*Primary Aim 3: Consumer perspectives:* To compare the acceptability and perceived benefit of each model of care from the perspective of both pregnant women and their healthcare providers.

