### Hypotheses

We hypothesize that the PIPA model of care will be at least 15% more clinically effective, and will be more economically efficient and acceptable, than ‘care as usual’. Secondly, we expect that each of the screening measures will have acceptable psychometric characteristics when used in this population of pregnant women.

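### Bootstrap intervals on the ICERs for Primary Aim 2 cannot be read if replicates straddle zero effect or PIPA is cheaper and better, and the effect has no stated denominator

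*Protocol article*

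**What the plan says.** The Cost-effectiveness analysis section of the protocol article defines the effect: "The primary outcome variable for the cost-effectiveness analysis (Primary Aim 2) will be the proportion of ‘correct’ referrals initiated and ‘incorrect’ referrals averted". It does not say what the proportion is a proportion of.

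Uncertainty is summarised on the ratio scale: the ICERs are to be "represented with 95% confidence intervals for the ICERs using non-parametric bootstrapping techniques". The sensitivity analysis has the same target: "One-way and multivariate probability sensitivity analysis using Monte Carlo simulations across the cost and effect distributions will be undertaken to investigate uncertainty around the ICERs".

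Aims, Primary Aim 2, treats two ratios as separate results: "the incremental cost per ‘correct’ referral made and the incremental cost per ‘incorrect’ referral averted by the PIPA model compared to the SAFE START model".

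On direction, the analysis section says "The incremental costs and effects of SAFE START compared to PIPA will be expressed as the incremental cost-effectiveness ratio (ICER"), whereas Aim 2 has the increment "by the PIPA model compared to the SAFE START model".

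Hypotheses expects PIPA to be at least 15% more clinically effective and says it "will be more economically efficient and acceptable" than care as usual.

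**The concern.** A confidence interval for an ICER is easy to read in one situation: essentially all replicates lie in the same trade-off quadrant, for example dearer and better. The protocol gives reasons to expect something else. Background says that the SAFE START threshold may lead to over-servicing and higher costs, and Table 1 restricts MCD referral under PIPA to the highest risk level. Cheaper and better is therefore a plausible result, and there the size of the ratio ranks nothing. A small or uncertain effect causes a different problem: the denominator of the ratio changes sign between replicates.

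The missing denominator adds to this. Depending on how the proportion is read, the two ICERs of Aim 2 are either one result reported twice or two results that may disagree. Either way, a primary aim could report intervals that do not show whether PIPA is more efficient.

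**Working it through.** The article gives no ICER, cost, SD or referral rate, so there is no figure of its own to reproduce. Taken from the document: a difference of 15 points (Hypotheses; Statistical analysis), 120 + 120 + 50 = 290 timed referrals per model, and 3500 women per model (both from Participant eligibility and expected sample sizes). All costs, SDs, SEs, referral rates, correct shares and values per referral below are assumptions. Differences are PIPA minus SAFE START, in AUD.

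**1. Order of negative ratios.** ICER = ΔC/ΔE.

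| ΔC | ΔE | ICER |
|---|---|---|
| -10 | +0.05 | -200 |
| -10 | +0.15 | -66.7 |
| -10 | +0.30 | -33.3 |
| -20 | +0.15 | -133.3 |
| +10 | -0.15 | -66.7 |

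A larger gain moves the ratio towards zero, and a larger saving moves it away. A dominant result (row 2) and a dominated one (row 5) give the same value.

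**2. Bootstrap at n = 290 per model** (10,000 resamples, percentile limits). Assumed: SAFE START mean cost 60, SD 30, correct share 0.60. Rounding to whole referrals makes the gains 44/290 = 0.152 and 14/290 = 0.048.

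| Scenario | Cheaper and better | Other quadrants | 95% interval for ICER |
|---|---|---|---|
| ΔC -10, gain 0.152 | 99.98% | almost none | -143 to -33 |
| ΔC -3, gain 0.152 | 89% | 11% dearer and better | -66 to +13 |
| ΔC -10, gain 0.048 | 88% | 11% cheaper and worse | -1616 to +1366 |
| ΔC +10, gain 0.048 | 0% | 88% dearer and better, 11% dearer and worse | -1286 to +1616 |

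In the last two rows the remaining resamples have almost all exactly zero effect. The last row shows that straddling zero effect spoils the interval whether PIPA is cheaper or dearer.

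A second simulation used normal draws with ΔC -5 (SE 3). A gain of 0.05 (SE 0.04) gives about -1040 to +830, and a gain of 0.15 (SE 0.04) gives -98 to +6.

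**3. Net benefit from the same resamples.** INMB = λΔE - ΔC, where λ is the value per correct referral. For ΔC -10 and gain 0.048, λ = 100 gives 14.8 (5.5 to 24.1). For ΔC -10 and gain 0.152, λ = 0, 100 and 200 give 10.1 (5.5 to 14.7), 25.2 (16.1 to 34.1) and 40.4 (24.3 to 56.1). These limits are ordered, and higher is always better.

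**4. Denominator.** The definitions allow two classes of referral, the second being "a clinically inappropriate referral made by the midwife, as determined by the consensus opinion of senior psychosocial clinicians".

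- *Referrals* (one reading of Primary Aim 1, item ii). Incorrect share = 1 - correct share, so the gain in correct equals the incorrect averted (0.15 = 0.15). The two ICERs are identical in every resample.
- *Women assessed* (one reading of the Time 3 text and of the clinical effectiveness analysis, both of which speak of women). With r the referral rate and p the correct share, correct per woman = r·p and incorrect per woman = r·(1 - p). Take p = 0.60 and 0.75, and ΔC = -5 per woman:

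| Referred, SAFE START vs PIPA | Δ correct | Incorrect averted | ICERs |
|---|---|---|---|
| 30% vs 30% | +0.045 | 0.045 | -111 and -111 |
| 30% vs 25% | +0.0075 | 0.0575 | -667 and -87 |
| 30% vs 20% | -0.03 | 0.07 | +167 and -71 |

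In the middle row, with 3500 women per model, the SE of the correct-referral effect is √(0.18·0.82/3500 + 0.1875·0.8125/3500) = 0.0093. Then z = 0.0075/0.0093 = 0.81, and about 21% of replicates have a negative effect. On the per-woman reading a near-zero effect is possible even when the correct share among referrals rises by 15 points.

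**The case against.** Several points on the other side stand.

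- A reader might infer that the trial hypothesises a cheaper PIPA and that its intervals are therefore bound to fail. Hypotheses speaks only of greater economic efficiency. The added severity and self-harm questions could raise assessment cost, and dearer-and-better also fits the hypothesis. An ICER interval is standard there.
- At a clear 15-point gain the upper limit can be read. When every replicate has ΔE > 0, ICER < λ is equivalent to INMB > 0, so an upper limit of +6 means that 97.5% of replicates favour PIPA at AUD 6 per correct referral. Only the lower limit lacks meaning.
- A reader might conclude that the two ICERs must be the same number. That holds only if the denominator is referrals, and the text does not settle this.
- The reversed direction might look like a reversed result. Both differences change sign, so the ratio and its interval are unchanged, and the sentence after the reversed one already puts PIPA relative to SAFE START.
- The article does not say percentile bootstrap. Cost-effectiveness planes and acceptability curves may be in a fuller plan that is not shown, so their absence alone is no fault.

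What remains concerns stated text: the article itself chooses the ratio interval as its summary, points the Monte Carlo analysis at the same ratio, and leaves the effect open to two readings with different results.

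**Conclusion.** The point holds as a conditional weakness that is cheap to correct. The planned interval cannot be read if replicates straddle zero effect, and its lower limit has no meaning if PIPA is cheaper and better. It remains usable if PIPA is clearly dearer and better. In the illustrations the interval ranges from tidy (-143 to -33) to unreadable (-1616 to +1366), depending mainly on how far the effect lies from zero. The undefined denominator makes the two ICERs of Aim 2 either identical or potentially opposite in sign (+167 and -71). The direction wording is a slip with no effect on the ICER. These sizes rest on assumed costs, SDs, SEs, referral rates and correct shares. The algebra on ordering and on the denominator does not.

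**What to change.** State in the cost-effectiveness section that both effects, correct referrals made and incorrect referrals averted, are counted per woman assessed. If correctness is judged only on a sample of referrals, each effect is the referral rate times the relevant share, and both parts should be resampled.

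Take every difference as PIPA minus SAFE START, and align the reversed sentence with Aim 2.

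From the same bootstrap replicates, report the differences in cost and in each effect with the share of replicates in each quadrant. Add incremental net benefit with a 95% CI, or an acceptability curve, over a stated range of values per referral. Quote an ICER interval only where the replicates lie in one trade-off quadrant. Otherwise report dominance, or that the replicates cross quadrants.

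The change costs some analysis wording and needs no new data. The real downside is that a range of values per correct referral and per incorrect referral averted has to be chosen and shown, and the article supplies none.
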